**Methods:**

Prospective cohort study involving 13 hospitals in Spain with a follow-up period of up to 5 years after diagnostic biopsy. Eligibility criteria: Patients diagnosed with breast cancer between April 2013 and May 2015 that have consented to participate in the study. Data collection: Data will be collected on the following: pre-intervention medical history, biological, clinical, and sociodemographic characteristics, mode of cancer detection, hospital admission, treatment, and outcomes up to 5 years after initial treatment. Questionnaires about quality of life (EuroQoL EQ-5D-5 L, the European Organization For Research And Treatment Of Cancer Core Quality Of Life Questionnaire EORTC QLQ-C30 join to the specific breast cancer module (QLQ-BR23), as well as Hospital Anxiety and Depression Scale were completed by the patients before the beginning of the initial treatment and at the end of follow-up period, 2 years later. The end-points of the study were changes in health-related quality of life, recurrence, complications and readmissions at 2 and 5 years after initial treatment. Statistical analysis: Descriptive statistics will be calculated and multivariate models will be used where appropriate to adjust for potential confounders. In order to create and validate a prediction model, split validation and bootstrapping will be performed. Cost analysis will be carried out from the perspective of a national health system.

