### Sample size calculation

We estimated the sample size based on the objective related to the creation and validation of a predictive model for which a relatively large sample size is required. The literature on prediction models indicates that a minimum of 10 outcome events are needed per predictor (relapse) [24]. Our aim is to include a limited but comprehensive list of variables (likely, not less than 10), in the multivariate regression models. Given this, we estimated that we needed at least 100 events of the dependent variable in the sample in order to ensure that the regression model converges adequately. It has been reported [25] that 7% of patients with breast cancer relapse within the first 2 years and considering this rate, we calculated the estimated sample size. Nevertheless, so far, based on 1456 patients, the relapse rate has been 4%, implying that no more than six variables should be included in the predictive models. We included all consecutive new cases until the sample size was achieved.

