### Statistical analysis

- Descriptive statistics: Mean and standard deviations for continuous variables (or median and interquartile ranges, when the observed variables do not follow a normal distribution) and frequencies and percentages for qualitative variables.-Bivariate analysis:The Student’s t-test or the non-parametric Wilcoxon test (for non-normal distributions) will be applied for two-level outcomes, and ANOVA analysis or a Kruskal–Wallis test (for non-normal distributions) where there are three or more categories in the outcome. Otherwise, for categorical variables, the Chi-square test (or Fisher’s Exact method, where required) will be used. Multivariate models will be used where appropriate to adjust for confounders.-Creation and validation of predicitive models:. Participants will be randomly divided into two groups: the derivation (60%) and validation (40%) cohorts. The study unit will be the patient (each patient being included only once). The predictive model will be created with the derivation group (group 1). Initially, univariate analyses will be performed, to identify variables related to the selected outcomes. Variables with a *p* < 0.20 will be entered into a multivariate logistic regression model, when outcome variables are dichotomous (mortality, re-admissions or relapse, major complications). Statistically significant variables will be included in the final model. Based on its estimated contribution in the multivariate logistic regression model, a score will be assigned to each variable. From this, a severity risk score will be created with the receiver operating characteristic curve. One cut-off point will be selected, namely, that giving the best balance between sensitivity and specificity. For the continuous outcomes (changes in health-related quality of life), a general lineal model will be used. The validity of the model and the score will be tested in the validation sample (group 2) and also in the retrospective sample (group 3). We will calculate the sensitivity, specificity, and area under the receiver operating characteristic curve (AUC), and *p* values for comparisons of AUCs between the groups. The models will be calibrated using the Hosmer-Lemeshow test. A multilevel analysis will be performed with patients (level 1) nested within hospitals (level 2).

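### The sample size is said to cover validation but is set for model fitting only, and the planned p value between AUCs cannot show that discrimination is preserved in about 23 validation relapses

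*Protocol article*

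**What the plan says.** In the protocol article, Sample size calculation ties the size to both tasks: "We estimated the sample size based on the objective related to the creation and validation of a predictive model". The criterion that follows is "a minimum of 10 outcome events are needed per predictor (relapse"). With about ten predictors in view, this becomes "we needed at least 100 events of the dependent variable in the sample". The planned two-year relapse rate is 7%. The section then reports a rate of 4% so far in 1456 patients and limits the models to six variables.

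Statistical analysis sets the split: "Participants will be randomly divided into two groups: the derivation (60%) and validation (40%) cohorts". Variables pass a univariate screen at p < 0.20, and those that are significant in the multivariate model are kept, all within the derivation group (group 1). The model and score are then tested in the validation group (group 2) and in the retrospective cohort (group 3). The listed measures are sensitivity, specificity, the AUC and "p* values for comparisons of AUCs between the groups", followed by a Hosmer-Lemeshow test.

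The abstract adds that "split validation and bootstrapping will be performed". The Statistical analysis section gives bootstrapping no role.

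**The concern.** There are two linked problems.

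First, events per predictor is a rule for fitting a model. It says nothing about how precisely performance can be estimated in women who were not used for fitting. It is also counted over the whole sample, although only 40% of the women go into validation. The size therefore contains nothing for validation, although the section says it does.

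Second, the one inferential statement about discrimination is a test of no difference between AUCs. A non-significant result from so few events mostly reflects the small number of events. The null hypothesis is also poorly chosen. The derivation AUC is measured in the same women in whom variables were selected and coefficients fitted, so it is optimistic and some fall is expected even for a sound model.

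The Discussion (Expected outcomes of the study) intends these rules as the basis for software used by physicians and patients. If p > 0.05 is taken as confirmation, a rule that has lost a material part of its discrimination could be put into use as though its derivation AUC had been confirmed.

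**Working it through.** **The plan's own figures.** These reproduce:
- 10 predictors × 10 events = 100 events.
- 100 / 0.07 = 1429 women. The article prints no target number; 1456 valid patients is within 2% of this.
- 1456 × 0.04 = 58.2 events, and 58.2 / 10 = 5.8, rounded to six variables.

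**Events after the split** (1456 women, 60/40):

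| | Derivation (874 women) | Validation (582 women) |
|---|---|---|
| Relapses at 4% | 873.6 × 0.04 ≈ 35 | 582.4 × 0.04 ≈ 23 |
| Relapses at 7% | 873.6 × 0.07 ≈ 61 | 582.4 × 0.07 ≈ 41 |

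**Standard error of an AUC (Hanley-McNeil).** With AUC A, e events and n non-events, Q₁ = A/(2−A) and Q₂ = 2A²/(1+A):

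SE² = [A(1−A) + (e−1)(Q₁−A²) + (n−1)(Q₂−A²)] / (e·n)

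At 4% relapse:
- Derivation, A = 0.80, e = 35, n = 839: Q₁ = 0.667, Q₂ = 0.711, SE = 0.045.
- Validation, A = 0.70, e = 23, n = 559: Q₁ = 0.538, Q₂ = 0.576, SE = 0.062.
- Half-width of the 95% interval for the validation AUC: 1.96 × 0.062 ≈ 0.12. At 7% it is 1.96 × 0.047 ≈ 0.09.

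**Power of the AUC comparison.** The groups are independent, so the SE of the difference is √(0.045² + 0.062²) = 0.077. The two-sided 5% level is an assumption, since the article gives none.

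Power ≈ Φ(0.10/0.077 − 1.96) = Φ(−0.66) ≈ 25%.

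The same calculation for other assumed AUCs:

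| True AUC, derivation to validation | Power at 4% | Power at 7% |
|---|---|---|
| 0.80 to 0.75 | 10% | 14% |
| 0.80 to 0.70 | 25% | 40% |
| 0.75 to 0.60 | 47% | 70% |
| 0.80 to 0.50 | 98% | >99% |
| 0.75 to 0.50 | 89% | 99% |
| 0.70 to 0.50 | 71% | 91% |
| 0.65 to 0.50 | 47% | 69% |
| 0.60 to 0.50 | 24% | 37% |

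The loss detectable with 80% power is about 0.22 at 4% relapse and about 0.17 at 7%.

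**Check by simulation.** With binormal scores, an unpaired DeLong test and 2000 runs, power for a 0.10 loss (derivation AUC 0.70 to 0.85) was 26% to 36% at 4% and 42% to 59% at 7%. This is somewhat higher than the formula gives but leads to the same conclusion.

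**Group 3.** The retrospective cohort has 1086 women, and the article gives no event rate for it. With assumed rates of 4% to 20% and 35 derivation events, power for a fall from 0.75 to 0.65 is about 32% to 47%. The larger cohort helps little, because the derivation AUC is itself imprecise.

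**The case against.** The strongest reply is that the article never says p > 0.05 means validated. The p value stands beside the validation AUC, sensitivity, specificity, a Hosmer-Lemeshow test and an external cohort. This is correct. A reader might infer that validity is decided by the p value, but the text contains no such rule.

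A reader might also infer that a useless score could pass as validated. The figures do not support this in general. A fall from 0.80 to 0.70 leaves a weaker score, not a useless one, and a collapse from 0.75 or 0.80 to 0.50 would be detected with 89% to 98% power at 4% relapse. Only a score that was modest in derivation (0.60 to 0.70) could fall to 0.50 and often escape the test, with power of 24% to 71%. In 300 simulated trials using the plan's selection steps on 30 pure-noise candidates, the test was non-significant in about 52% of runs that yielded a model. But the mean validation AUC was about 0.51, and the plan reports that AUC. Thirty pure-noise candidates is also an assumption far from a list that includes stage, nodes and receptor status.

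Three further replies deserve an answer:
- Optimism in the derivation AUC widens the expected difference and makes rejection more likely. This is true, and it means the test can also fault a sound model for ordinary optimism. In neither direction does it answer the question of interest.
- The 25% applies to relapse at 4%, a rate reported as so far observed. Event rates for mortality, readmission and major complications are not given, and five-year follow-up would add events if it is funded. This limits the scope of the figure. At the planned 7%, power is still only about 40%.
- A condensed article may leave bootstrap details and confidence intervals to a fuller document. This is accepted, and their absence is not the point. The point is that the article fixes a poorly suited comparison and describes the sample size as covering validation.

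**Conclusion.** The point holds in a limited form. The size was set for model fitting alone, although the section names validation as well. At 4% relapse, validation rests on about 23 events and an AUC known to about ±0.12. The between-group p value has about 25% power for a fall from 0.80 to 0.70 at 4% relapse and about 40% at 7%, so a non-significant result is not evidence that discrimination is preserved. The risk of misreading is greatest where the derivation AUC is about 0.60 to 0.70.

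This rests on relapse as the outcome, the group 1 against group 2 comparison, a two-sided 5% level, the assumed AUCs, and all 1456 women contributing. Excluding in situ cases or women with incomplete data would lower the event counts and the power. The change should be made, but the flaw does not invalidate the other validation measures.

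**What to change.** In Statistical analysis, replace the p values for AUC comparisons with the AUC and its 95% confidence interval in each validation sample (group 2 and group 3). Add the optimism-corrected AUC, obtained by bootstrapping the whole procedure (screen, selection and fitting), which gives the abstract's commitment a defined role. State that validity will be judged on these estimates and intervals and not on the absence of a significant difference.

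In Sample size calculation, state that the size was set for model creation only. Give the expected validation events (about 23 at 4%, about 41 at 7%) and the resulting AUC precision (about ±0.12 and ±0.09).

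No new data are needed. The cost is revised wording, some computing, and a reported AUC somewhat lower than the apparent one.

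### The only calibration method stated is the Hosmer-Lemeshow test, which neither calibrates a model nor measures miscalibration, and says little at about 23 validation relapses

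*Protocol article*

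**What the plan says.** The Statistical analysis section of the protocol article splits the cohort: "Participants will be randomly divided into two groups: the derivation (60%) and validation (40%) cohorts". The model and score built in the first part are to be tested in the second (group 2) and in the retrospective cohort (group 3). On calibration there is one sentence: "The models will be calibrated using the Hosmer-Lemeshow test". The other measures listed are sensitivity, specificity, AUC and p values comparing AUCs, which describe discrimination or classification. The abstract mentions bootstrapping but does not link it to calibration. No calibration intercept, slope, plot or recalibration step is named. The number of risk groups, the degrees of freedom and the sample in which the test is run are not stated.

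The Sample size calculation section gives the event rate: "based on 1456 patients, the relapse rate has been 4%, implying that no more than six variables should be included in the predictive models". Under Expected outcomes of the study, the rules are intended for software that lets physicians and patients weigh a woman's own risk.

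**The concern.** The sentence assigns the test a job that it cannot do. Hosmer-Lemeshow compares observed with expected counts across risk groups and returns a p value. It corrects no coefficient, and it does not show whether risks are too high, too low or too extreme, or by how much.

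This matters because absolute risk is the intended product, and AUC says nothing about whether a predicted 6% means 6%. Two kinds of miscalibration are plausible here:

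- **Overfitting.** The derivation part has few relapses and variables are selected by significance, which tends to make predicted risks too extreme (calibration slope below 1).
- **A shift in baseline risk.** The retrospective women came from a screening programme, were diagnosed in 2000 to 2008, and did not include symptomatic cases (Background).

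A single p value cannot tell these apart. With few events, a non-significant one is also weak evidence that neither is present.

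**Working it through.** **Inputs from the article.** N = 1456, relapse rate so far 4%, split 60/40, 10 events per predictor, planned 2-year relapse rate 7%, target of at least 100 events.

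**The plan's own figures.**
- 1456 x 0.04 = 58.2 events, and 58.2 / 10 = 5.8. This agrees with the stated limit of six variables.
- 100 / 0.07 = 1429 women, close to the 1456 valid patients.

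**Events after the split.**
- Derivation: 1456 x 0.60 x 0.04 = 34.9 relapses.
- Validation: 1456 x 0.40 = 582 women, and 582.4 x 0.04 = 23.3 relapses, or about 2.3 per decile of risk.
- At the planned 7%, validation would have 582.4 x 0.07 = 40.8 relapses.

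**Behaviour of the test in group 2.** This was simulated with 582 women, a mean true risk of 4%, a nominal 5% level and predictions fixed in advance. Assumptions not in the article: a normal linear predictor with SD 0.85 (AUC about 0.72) and ten groups unless stated. With g groups and fixed predictions in new data, the reference has g degrees of freedom (df); g-2 is the convention for the sample in which the model was fitted.

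| Situation | Hosmer-Lemeshow, 10 groups, 10 df | Test aimed at that feature |
|---|---|---|
| Perfect calibration | about 7% | nominal 5% |
| True slope 0.8 | about 18% | slope test, about 14% |
| True slope 0.7 | about 33% | slope test, about 36% |
| Mean predicted 6%, true 4% | about 4% | intercept test, about 54% |

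**Sensitivity to the assumed AUC.** Over AUC 0.69 to 0.81 (ten groups, 10 df), rejection is 14% to 32% at slope 0.8, 23% to 52% at slope 0.7, and 75% to 93% at slope 0.5. For 6% predicted against 4% true it is 3% to 6%. Only gross overfitting is found reliably.

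**Reference distribution.** With ten groups about nine expect fewer than 5 events. Under perfect calibration the rejection rate is about 7% with 10 df and about 12% with 8 df. With about five groups and 5 df it is about 4% to 6%.

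**What an interval would show.** With 23 observed and 23 expected events, the exact Poisson 95% interval for observed/expected runs from about 0.63 to 1.50. A non-significant p value hides that width.

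**The case against.** The strongest reply is that low power comes from having 23 events, not from choosing Hosmer-Lemeshow. This stands for the slope: a test on the calibration slope does about the same (14% against 18% at 0.8, 36% against 33% at 0.7). A reader might infer that changing the method would find overfitting more often; the figures do not support that. The reply fails for a shift in mean risk, where the intercept test rejects in about 54% of runs and Hosmer-Lemeshow in about 4%. It also does not touch the main argument, which is estimation rather than testing and holds at any event count.

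A reader might also infer that the test's chi-square reference is invalid here. The article does not support that, because it fixes neither the number of groups nor the degrees of freedom. Size is somewhat liberal with ten groups and 10 df, wrong if g-2 df is carried over to validation data, and near nominal with about five groups and g df.

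Nor do 23 events describe every validation. They apply to relapse at the rate reported so far, in group 2. Mortality, readmissions, major complications, 5-year outcomes and the retrospective sample of 1086 women will have other counts, which are not given.

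Finally, an article condenses a fuller plan, it commits to TRIPOD reporting, and it states no rule that a non-significant test means good calibration. These points soften the concern without removing it. The sentence names a method for a purpose it does not serve, and neither TRIPOD nor the bootstrapping is tied in the text to an intercept or slope.

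**Conclusion.** The point holds in a limited form and should be acted on. The only stated calibration method does not calibrate and does not quantify miscalibration, while the tools are meant to convey absolute risk. For relapse in the 40% split, at about 23 events, a non-significant result would be the usual outcome under a slope of 0.8 (about 82% of runs, 100 - 18) and under a 50% overstatement of mean risk (about 96%, 100 - 4). These percentages rest on ten groups, 10 df, an AUC of about 0.72 and the 4% rate. They move with those assumptions, as the ranges above show. The event count and the unsuitability of the test as a measure of calibration do not depend on the simulation.

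**What to change.** Replace the sentence with: *Calibration will be assessed in groups 2 and 3 by calibration intercept (calibration-in-the-large) and calibration slope with 95% confidence intervals and a smoothed calibration plot; the Hosmer-Lemeshow test is descriptive only.*

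If the test is kept, state the number of groups and use g degrees of freedom in validation data.

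If coefficients are to be shrunk, take the factor from the bootstrap in the derivation data, not from group 2 or 3. Under perfect calibration, slope estimates in group 2 range from about 0.49 to 1.58 (central 95% of the simulation), so shrinking by that estimate could nearly halve or greatly inflate the coefficients by chance. It would also end that sample's use as an independent test.

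The cost is wording and two further estimates and a plot per model and sample, from data already collected. The downside is that intervals will be wide and power to detect a wrong slope will be no better than now.

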Cost analysis: The perspective of the cost analysis is that of a public hospital in a national healthcare system, and therefore, only direct medical costs (DMCs) will be included. DMCs will be derived from healthcare use registered in the medical records. Data on resource use will be obtained for the periods of 24 and 60 months after baseline, that is, since diagnosis. This includes data on medical visits; hospital admissions; laboratory tests, imaging studies, and other diagnostic procedures; and treatments including surgery, medication (chemotherapy and other) and radiotherapy. Little used and/or low cost resources will be not considered. The value of resources used by patients is to be calculated in terms of the relevant unit costs and the average cost per patient in the sample. The unit costs will be obtained for each resource from the accounting system of participating hospitals. Unit costs will be multiplied by the resource quantities to obtain the annual cost for each patient. All costs will be assigned in euros of the year in which the resource has been used; no discount rate will be needed due to the short time horizon.

Costs will be aggregated and classified according to the following categories: outpatient clinic visits (number of visits to specialists); hospitalization (total length of hospital admissions, length of stay in intensive care unit and day hospital visits); laboratory tests (laboratory tests performed through ambulatory care); and imaging studies (ultrasonography, axial computerized tomography, magnetic resonance, radiography and other imaging studies related to the diagnosis, and treatment and associated complications); diagnostic procedures (procedures related to the monitoring of the disease and associated complications); surgery (surgical procedures related to the treatment and associated complications); medication; radiotherapy.

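### Costs are valued in euros of the year of use with no common price year, left undiscounted even at 60 months, and may omit rare but expensive resources

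*Protocol article*

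**What the plan says.** The cost analysis in the Protocol article (Statistical analysis) fixes three rules.

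- **Price level.** "All costs will be assigned in euros of the year in which the resource has been used; no discount rate will be needed". No reference year and no price index are given.
- **Discounting.** "no discount rate will be needed due to the short time horizon". The same section sets the horizons: "Data on resource use will be obtained for the periods of 24 and 60 months after baseline, that is, since diagnosis".
- **Omission.** "Little used and/or low cost resources will be not considered". No cut-off is given. Among the cost categories, hospitalization includes "length of stay in intensive care unit and day hospital visits".

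On the form of the result, the section says "Unit costs will be multiplied by the resource quantities to obtain the annual cost for each patient". It also refers to an average cost per patient in the sample, and adds "Costs will be aggregated and classified according to the following categories".

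Table 1 gives the purpose: average costs of breast cancer care, differences between regions, and the most efficient processes and treatments.

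**The concern.** Each rule is a positive choice, so none is a detail left for a fuller plan to supply.

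- **Price level.** Euros of different years do not have the same value. An average over women diagnosed up to two years apart, or over several years of follow-up, mixes price levels, and the result belongs to no stated year.
- **Discounting.** One reason, the shortness of the horizon, covers both 24 and 60 months. It suits the first far better than the second.
- **Omission.** With *and/or*, low frequency alone is enough to exclude a resource. A resource's contribution to mean cost is its frequency times its price, so a rare but dear item can matter more than a common cheap one.

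At stake is the interpretation of the third study objective: the average cost, and any comparison of costs between regions, processes or treatments.

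**Working it through.** The article gives no cost figure, inflation rate or discount rate, so there is no figure of its own to reproduce. The rates, cost profiles and relative prices below are assumptions.

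**Inputs from the article**
- Recruitment from 15 April 2013 to 20 May 2015 (Design and setting), about 2.1 years.
- Horizons of 24 and 60 months from diagnosis (Statistical analysis, cost analysis).
- Observed relapse of 4% so far (Sample size calculation).
- Stage IV disease in 18 + 11 = 29 of 1456 women, or 2.0% (Table 3).

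**1. Calendar span.** The last woman reaches 24 months in May 2017 and 60 months in May 2020. Use therefore spans 2013-2017 (five calendar years) or 2013-2020 (eight).

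**2. Price drift.** The cost ratio for identical care is (1 + i)^years, with i the assumed yearly price growth.

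| Comparison | Years | i = 0% | i = 1% | i = 3% |
|---|---|---|---|---|
| 2013 vs 2017 | 4 | 0% | 1.01^4 = 1.041, 4.1% | 1.03^4 = 1.126, 12.6% |
| 2013 vs 2020 | 7 | 0% | 1.01^7 = 1.072, 7.2% | 1.03^7 = 1.230, 23.0% |
| First vs last woman recruited | 2.1 | 0% | 1.01^2.1 = 1.021, 2.1% | 1.03^2.1 = 1.064, 6.4% |

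The third row matters for comparisons between women. Much of the drift in the second row happens within each woman's own follow-up and is common to all.

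**3. Discounting.** Present value = sum of w_t/(1 + r)^t for t = 0 to 4, where w_t is the share of cost in each year of follow-up and the first year is undiscounted. The overstatement is 1/(present value) - 1.
- Even profile, r = 3%: (1 + 0.971 + 0.943 + 0.915 + 0.888)/5 = 0.943, and 1/0.943 = 1.060, so 6.0%.
- Front-loaded profile (60/15/10/8/7%), r = 3%: 0.600 + 0.146 + 0.094 + 0.073 + 0.062 = 0.975, so 2.5%.
- At r = 5%: 10.0% (even) and 4.1% (front-loaded).
- With r from 1.5% to 5%, and a back-loaded profile (10/15/20/25/30%) included, the range is 1.3% to 12.7%.
- Over 24 months only, the same rates and profiles give 0.3% to 2.9%.

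**4. Omission.** Let a share f of women use a resource whose price is c times the mean of all other costs. The share of mean cost lost by dropping it is fc/(1 + fc).
- f = 1%: c = 1 gives 0.01/1.01 = 1.0%; c = 5 gives 0.05/1.05 = 4.8%.
- f = 4% (the observed relapse frequency, as an illustration): c = 1 gives 0.04/1.04 = 3.8%; c = 5 gives 0.20/1.20 = 16.7%.
- c = 0.1 and f = 1%: 0.1%, which is negligible.

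As a simple contrast, an item used by 1% of women at an assumed 10,000 euros adds 0.01 × 10,000 = 100 euros to the mean. An item used by every woman at 50 euros adds 50. Frequency alone ranks them the wrong way round.

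**The case against.** The strongest reply has four parts.

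- **No 60-month total is stated.** The section describes an annual cost per patient. This stands, and summation over 60 months is an inference. It does not remove the price-year problem: an average annual cost over women who entered up to 2.1 years apart already mixes price years.
- **The firm stage is 24 months.** Duration of the project makes the 5-year stage depend on funding, and Expected outcomes of the study says that the article details the 2-year protocol. At 24 months, leaving out discounting changes little. This also stands, and it limits the discounting point to the 60-month analysis. The cost section nevertheless already plans 60-month data and applies the same reason to it. The price-year point does not depend on that funding.
- **Later indexation is not ruled out.** This is possible, but the written rule values costs in the year of use and mentions no conversion. Followed as written, it mixes price levels.
- **Intensive care is a named category, and relapse treatment would fall under surgery, medication or radiotherapy.** This stands. A reader might infer that intensive care stay or relapse treatment will be dropped; the article does not say so. What remains is that the omission rule and the category list are not reconciled, and that the rule has no cut-off.

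**Conclusion.** The three costing rules are badly fixed, and the point holds as a should-fix.

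- **Price year.** No common price year is set, for either horizon. At an assumed 1-3% yearly growth, price levels mixed in the analysis differ by about 4-13% (2013 vs 2017) or 7-23% (2013 vs 2020). Between the first and last women recruited the gap is about 2-6%. At zero inflation all of these vanish.
- **Discounting.** The stated reason is acceptable at 24 months and weak at 60, where an undiscounted total would be about 2.5-6% too high at an assumed 3%.
- **Omission.** The rule permits loss of rare, expensive items. The error can only be downward. Its size ranges from negligible to material, depending on frequencies and prices that the article does not give.

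A reader might go further and conclude that the average and regional costs will be wrong, or that late-recruited women or particular regions will look dearer by up to 23%. The article does not support that. The sizes rest on assumed rates. The gap between women is bounded by the 2.1-year recruitment window. Regional bias from price years or discounting would need regions to differ in the calendar timing of care or in their cost profiles, and from omission it would need them to differ in use of the dropped items. The article gives one overall window and no dates by region.

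**What to change.** Amend the cost section in three places.

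1. **Price year.** Express all costs in one stated price year, either by a published price index or by applying one year's unit costs to all quantities.
2. **Discounting.** Keep the 24-month analysis undiscounted. In the 60-month analysis, discount costs after month 12, for example at 3%, with 0% and 5% as sensitivity analyses.
3. **Omission.** Allow a resource to be left out only when quantity times unit cost is below a set small share of total cost, for example 1%. State that the listed categories, including intensive care stay, are always costed.

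The cost is two or three sentences and a small amount of re-costing. Annual costs per patient are already planned, and Variables lists treatment dates and visits per year. It lists no dates for follow-up diagnostic tests, but the present rule already requires the year of use. Applying one year's unit costs to all quantities would remove that need for the price-year step. Discounting would still need the year of follow-up.
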